##### Pilot Test Compensation

To compensate for their time, we will provide each participant with a $25 gift card for completing and commenting on the AIMS survey.

### Study 3: Assessment of Variation in American Indian Mammography Satisfaction

#### Full AIMS Implementation Procedure

##### AIMS Recruitment

As with the focus group and AIMS pilot testing portions of this study, AIMS survey participants will be recruited at the Haskell Health Center through referral from clinic personnel and through posters in the waiting area. We will also recruit at 4-5 AI/AN community events held each year (one event in each of the four Kansas-based reservation cities (e.g., Horton, White Cloud, Mayetta, and Reserve, KS). These community events will include health fairs and Pow Wows. This multi-method plan of recruitment will allow us better access to participants who do not use IHS facilities for mammograms. In advance of events, we will post flyers and posters at various community locations in the four primary Kansas Indian Reservation sites and at the Haskell Health Center. We will also post informational flyers at other local AI/AN venues including the Heart of America Indian Center and the offices of the American Indian Council. We will make two Internet-ready laptop computers available at each community event so that interested participants readily may complete the AIMS survey. Postcards with the Healthy Living American Indian Women website address will be provided to those women who express interest but who prefer to complete the assessment in the comforts of another environment (e.g., their home or local library). An additional paper and pencil version of the AIMS survey will be available on site at community recruitment events for those individuals preferring a non-electronic information submission approach.

The Principle Investigator and Project Manager will maintain close contact with key community member stakeholders involved in the proposed recruitment venues and will conduct ongoing assessments of the feasibility of the procedure used to identify women for the AIMS survey. Appropriate adjustments in the recruitment protocol will be made to meet survey accrual needs.

Eight to 10 subjects per AIMS survey item will be used during this study (for example, if 25 items are included in the instrument, 200-250 patients will be used). We will mail postcard reminders and telephone persons who were recruited and expressed an interest in participating in the AIMS on their own time but who fail to engage with the survey to maximize recruitment efficiency and survey completion.

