### Access to Mammography

Access issues that may be classified as barriers to mammography include limited hours of operation, acceptance of self-referrals, ease of making an appointment, waiting room time, the use of reminder postcards or telephone calls, and location/type of facility. For the AI/AN population, this may also entail the pervasive unavailability of Indian Health Service practitioners and facilities. For example, all enrolled members of federally-recognized tribes are eligible for free health services at Indian Health Service (IHS) facilities and most AI/AN receive at least some of their care at IHS facilities. The IHS has 12 area offices overseeing 550 healthcare facilities across the US. The IHS does not have funding to place mammography machines in all clinics or to transport women to clinics that have them [57]. As such, many women go outside the IHS for screening.

A local IHS facility, Haskell Health Center (HHC) in Lawrence, KS (approximately 40 miles from the Kansas City Metropolitan area), serves approximately 8500 urban and rural (on- and off-reservation) AI/AN, and is administered by the Oklahoma City area office and staffed by a variety of medical professionals including physicians, nurses, pharmacists, and health education counselors. Their patient population represents over 200 AI tribes and over 30 AN villages. Although most patients live within 20 miles of HHC, some patients drive up to 70 miles for their medical services. HHC does not have mammography equipment. A third of their female patients are over age 40 and should, therefore, be having mammograms. A mobile unit from the Oklahoma office comes to HHC three days a year to serve these women.

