##### Participants

Twelve focus groups, each comprised of 8-12 unacquainted individuals, will be conducted. Focus groups will be conducted with American Indian/Alaskan Native women and will be stratified by residential location of participants (e.g., rural or reservation vs. urban). Participants will include women who are 40 years of age and older (in concordance with the American Cancer Society's recommended beginning age for annual screening of asymptomatic women) and will be further stratified by age (e.g., 40-64 year-olds and those aged 65 years and older). All participants will have had at least one mammogram performed within the past five years.

Focus group participants will be recruited at an Indian Health Service clinic through referral from clinic personnel and through posters in the waiting area. Participants who do not use the above-mentioned health service clinic may be more difficult to reach because there is no central location through which to reach them. We will post flyers and posters at various community locations in the four primary Kansas Indian Reservation sites located in Horton (Kickapoo), White Cloud (Iowa Tribe of Kansas and Nebraska), Mayetta (Prairie Band Potawatomi Nation), and Reserve (Sac and Fox Nation) Kansas. We will also post flyers at other local AI/AN venues including the Heart of America Indian Center and the offices of the American Indian Council. A brief questionnaire at the time of recruitment will allow us to assign groups based on the sampling frame illustrated in Table 2.

**Table 2 T2:** Focus Group Sampling Frame

AI/AN Women			
**Age 40-64**		**Age 65+**	

**Rural/Reservation**	**Urban**	**Rural/Reservation**	**Urban**

3 groups	3 groups	3 groups	3 groups

36 participants	36 participants	36 participants	36 participants

Focus group moderator's guides will be developed with input from program advisory board members and will be based partially on information from our prior mammography focus groups with Non-Hispanic White, Hispanic, and Black women. Discussions will focus on barriers to obtaining mammograms, motivating factors to obtain mammograms, past mammography experiences, and areas of mammography satisfaction and dissatisfaction.

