#### Development of an American Indian Mammography Satisfaction (AIMS) Survey

A mammography patient satisfaction survey was developed originally in 1991 by Cockburn and her colleagues [73]. This instrument includes 6 subscales: 1) convenience and accessibility, 2) staffs' interpersonal skills, 3) information transfer, 4) physical surroundings, 5) perceived technical competence of staff, and 6) general satisfaction. The reliability and validity of this instrument has been tested through research conducted in Australia. [name] mammography workgroup has also developed the Patient Assessment of Mammography Services (PAMS) mammography satisfaction for use with the general U.S. population. The PAMS survey assessed mammography satisfaction in the following areas: appointment scheduling, facility environment, exam, mammography technologist, mammography results reporting, and overall satisfaction. An additional open-ended question asked women to provide suggestions for improving the mammography experience. The Cockburn et al. and PAMS instruments will serve as the basis for our culturally tailored American Indian Mammography Satisfaction (AIMS) survey. We intend to modify and supplement these instruments by including questions that relate to the main themes and ideas generated through the focus groups that are not included in the Cockburn instrument. We will categorize questions into subscales and anticipate that additional subscales, beyond those included in the Cockburn instrument and our research team's PAMS survey, will include greater detail on facility access, hours of operation, acceptance of self-referrals, ease of making an appointment, location/type of facility, the use of reminder postcards or calls to patients, or the mode and timeliness of reporting exam results to patients. We will calculate patient satisfaction scores by numerically assigning each possible answer and summing answers within each scale. A global satisfaction score will be obtained by summing all subscale scores. We will also collect demographic data on participants' date of birth, education, marital status, income, employment status, race/ethnicity (e.g., American Indian, Alaskan Native, or mixed race), the number of mammograms obtained in the past, and history of breast malignancies. Our goal is to develop a brief instrument that can be administered easily.

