##### Web-Survey Technical Difficulties

Using a web application will ensure that all interested women will be able to access the AIMS survey. While most women will likely participate using laptop computers made available by the research team at recruitment events, a number of others will be more comfortable with accessing and completing the AIMS survey in the privacy of their own home. The minimum requirements will be a computer running an Internet Explorer version 4.0+ or equivalent and access to the internet. This includes more than 99% of all computers (browser usage from http://www.thecounter.com/stats/). Women who forget or lose their unique ID and password will be addressed by having users identify and answer "secret" questions upon their first visit to the site (e.g., First pet's name?). This information will be stored separate from study data. A participant who forgets her ID will be able to retrieve it by answering the questions she identified and answered.

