## Discussion

Mortality rates for breast cancer are rising in American Indian/Alaskan Native population and mammography rates are lowest in AI/AN. Understanding the mammography experiences and satisfaction with mammography of a heterogeneous AI/AN population is crucial to developing effective interventions to promote routine mammography utilization among this at-risk population. Over half of all AI/AN no longer live on reservations, but instead live in urban centers or, less so, in rural areas in heterogeneous groups [102]. To date, the AI/AN population in general has been understudied and the truly heterogeneous groups have in particular been left out of the literature. No systematic assessment of mammography experiences and satisfaction in a heterogeneous group that includes urban, rural, and reservation AI/AN has yet been undertaken. The data generated from this study can immediately be used to enhance the lack of data available on mammography satisfaction in the AI/AN population. The literature has shown variation in patient satisfaction studies [70,74]. We expect to find similar variations in the mammography experiences of American Indian/Alaskan Native women. The addition of culturally appropriate questions fueled by the focus groups (that were beyond those included in existing patient satisfaction instruments), will also likely uncover new variations not unearthed by prior research. The uniqueness of this study is highlighted by the fact that we will be able to assess the extent to which patient satisfaction varies among the American Indian/Alaskan Native population and whether satisfaction varies significantly when mammography services are accessed by American Indian/Alaskan Native women within or outside of Indian Health Service facilities. Any differences uncovered will be the catalyst for further study of American Indian/Alaskan Native women and future interventions to improve their mammography experience and alleviate mammography screening disparities.

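### Study 3 lists no residence item and compares IHS with non-IHS women without adjustment, so satisfaction by residence goes undescribed and a residence difference could enter the IHS contrast

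*Protocol article*

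**What the plan says.** All references are to the protocol article.

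- **Study 1, Participants and Table 2.** Focus groups "will be stratified by residential location of participants (e.g., rural or reservation vs. urban"). Table 2 gives six groups and 72 women to each residence stratum.
- **Discussion.** The stated gap is: "No systematic assessment of mammography experiences and satisfaction in a heterogeneous group that includes urban, rural, and reservation AI/AN has yet been undertaken".
- **Study 3, AIMS Recruitment.** Four to five community events a year are planned, with "one event in each of the four Kansas-based reservation cities". In addition, "AIMS survey participants will be recruited at the Haskell Health Center through referral from clinic personnel", and flyers go to "other local AI/AN venues including the Heart of America Indian Center and the offices of the American Indian Council". No urban target is set.
- **Web-Survey Technical Difficulties.** The authors expect that "most women will likely participate using laptop computers made available by the research team at recruitment events".
- **Development of the AIMS Survey.** "We will also collect demographic data on participants' date of birth, education, marital status, income, employment status, race/ethnicity", followed by number of past mammograms and history of breast malignancy. Type of residence is not in the list.
- **Mammography Satisfaction Variation.** The linear models name age and race/ethnicity and leave the list open. The IHS comparison is made by averaging global scores in each group, and likewise for subscales. No adjustment is described for it.
- **Aims and Sample Size Justification.** Aim 3 is variation among AI/AN women, and its only hypothesis is IHS versus non-IHS. The sample is 300 women, expected to split 30 to 270.

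**The concern.** The article treats residence as important enough to structure Study 1 and to define the project's novelty. It then leaves residence out of both the listed data and the described comparison in the quantitative study. Two consequences follow.

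First, the survey would give no account of satisfaction by residence, although the Discussion leads a reader to expect some description of urban, rural and reservation women.

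Second, the IHS contrast is observational. The named events are all in reservation cities, and AIMS Recruitment gives better access to women who do not use IHS for mammograms as the reason for recruiting by several routes. The other main route is the IHS clinic in Lawrence. If residence is associated with where the mammogram was done and also with satisfaction, a difference in raw averages mixes the two. The bias could run in either direction.

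**Working it through.** **1. The plan's own power figure.** Inputs from Sample Size Justification: n1 = 30, n2 = 270, d = 0.54, two-sided alpha 0.05.

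Noncentrality = d × √(n1·n2/(n1+n2)) = 0.54 × √(8100/300) = 0.54 × 5.196 = 2.806. With 298 df the critical t is 1.968, and power is 79.9% (80.1% by the normal approximation). The stated 80% is reproduced, and the point does not depend on it.

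**2. Size of a possible bias.** The protocol gives neither the urban share by IHS status nor the effect of residence on satisfaction, so both are assumed:
- difference in urban share between IHS and non-IHS groups, Δ = 0.20 to 0.40;
- residence effect on the global score, γ = 0.3 to 0.5 SD.

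Bias in the unadjusted contrast = Δ × γ. Rejection with no IHS effect comes from the noncentral t with noncentrality = bias × 5.196 (within-group SD taken as 1).

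| Δ | γ (SD) | Bias (SD) | Noncentrality | Rejection |
|---|---|---|---|---|
| 0.20 | 0.3 | 0.06 | 0.312 | 6.1% |
| 0.20 | 0.5 | 0.10 | 0.520 | 8.1% |
| 0.40 | 0.3 | 0.12 | 0.624 | 9.5% |
| 0.40 | 0.5 | 0.20 | 1.039 | 17.9% |

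**3. Cost of adjusting.** With a residence term, noncentrality = 2.806 × √(1 − R²), where R² is the squared correlation of residence with IHS status. This takes the residual SD as unchanged; any variance that residence explains would give some power back.

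| R² | Power at d = 0.54 | Detectable d at 80% power |
|---|---|---|
| 0.05 | 77.8% | 0.55 |
| 0.10 | 75.6% | 0.57 |
| 0.20 | 70.6% | 0.60 |
| 0.30 | 64.8% | 0.65 |

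To link this to step 2: R² = 0.1 × 0.9 × Δ² / [P(1 − P)], where P is the overall urban share. If 15% of non-IHS women are urban and Δ = 0.40, P = 0.1 × 0.55 + 0.9 × 0.15 = 0.19, R² = 0.0144/0.1539 = 0.094 and power is 75.9%. If 20% are urban and Δ = 0.20, P = 0.22, R² = 0.0036/0.1716 = 0.021 and power is 79.0%. Under the illustrative inputs the loss is therefore about 1 to 4 points.

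**4. Whether a residence description is feasible with 300 women.** The detectable difference at 80% power between urban and other women is 0.74 SD if 5% are urban, 0.54 if 10%, 0.41 if 20%, 0.35 if 30% and 0.32 if 50%. From a 10% urban share upward this is no coarser than the 0.54 SD that the plan accepts for its main contrast.

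**The case against.** A reader might infer that Study 3 **cannot** describe residence or separate it from IHS status. The documents do not support that. Table 3 makes a home address an eligibility criterion, and Study 3 mails reminders to women who have not started, so residence could be derived for at least some women. Step 4 shows the comparison is feasible unless urban women are very few. What remains is that Table 3 sits under pilot recruitment, and nothing says the address will be classified or analysed.

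A reader might also infer that the sample will be mostly reservation women. That is not established either. The Haskell clinic "serves approximately 8500 urban and rural (on- and off-reservation) AI/AN", flyers go to other venues, surveys can be completed at home, and the range of four to five events leaves one unnamed. The sentence on laptops concerns how the survey is completed, and attending an event in a reservation city does not show that a woman lives there.

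Recruitment route is also not the exposure. The contrast depends on where the mammogram was done. Haskell has no mammography equipment, and 90% of mammograms are expected to be non-IHS, so many women recruited at the clinic may fall in the non-IHS group. This stands: the association between residence and IHS status is plausible but unquantified.

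Aim 3 states no urban versus rural/reservation hypothesis, so the omission breaks no promised test. The confounding point does not need one. A residence-driven difference would also still be a real difference between the two groups of women. The step 2 rejection rates matter only if the contrast is read as reflecting IHS services.

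Finally, an article condenses its protocol and the covariate list is open-ended. That excuses an unnamed covariate. It does not fully answer an itemised data list without the factor that the same article uses to stratify Study 1.

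**Conclusion.** The point holds in a limited form. Residence structures Study 1 and defines the stated gap, but it is absent from Study 3's listed data and named covariates, and the IHS comparison is described without adjustment. Followed as written, Study 3 would not describe satisfaction by residence, and a residence difference could pass into the IHS contrast.

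The 0.06-0.20 SD bias and 6-18% rejection rate rest wholly on the assumed imbalance and residence effect. They show what is possible and do not estimate what will happen. The change is still worth making before data collection: it is cheap, and later recovery would depend on addresses that may be incomplete.

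**What to change.** - Add one residence item to AIMS (urban / rural off-reservation / reservation), checked against the home address where it is held.
- Tabulate residence against IHS status.
- Report global and subscale means by residence.
- Report the IHS contrast adjusted for residence beside the unadjusted one.
- The fifth yearly event that the four-to-five range allows could be held at an urban site.

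Residence-by-age enrolment minimums are not required. They are a debatable trade-off, and Aim 3 states no hypothesis that needs them.

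The cost is one more survey item and some loss of power for the adjusted contrast, as in step 3: small at R² of 0.05-0.10 and larger above that. Reporting both contrasts keeps the planned comparison intact. No additional women are needed.

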#### Data Analysis

##### Statistical Analysis

We will use means and standard deviations to summarize quantitative demographic information and frequencies. Percentages will be used to summarize categorical demographic information of the participants surveyed.

##### Internal Consistency

Data will be analyzed for internal consistency within domains to demonstrate the appropriate clustering of items. Each domain will be individually assessed using Cronbach's alpha, the standard statistical technique for assessing the coherency of each item within each domain.

##### Concurrent Validity

Concurrent validity is defined as the degree to which the scores on an instrument are related to the scores on another instrument administered at the same time, or to some other criterion variable at the same time. We will assess concurrent validity by correlating the sum of the subscale scores for each respondent with their score on the general scale.

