##### Construct/Discriminant Validity

Construct validity is the degree to which an instrument measures an intended construct. Multiple regression will be used to examine the discriminant validity of the proposed subscales and possible support for the multidimensional conceptualization of satisfaction. Scores on the general satisfaction subscale will be used as the outcome variables and other subscale scores will be used as predictor variables.

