##### Mammography Satisfaction Variation

We will use descriptive statistics to explore the extent to which the mammography experiences and mammography satisfaction of American Indian/Alaskan Native women vary. Frequencies and percentages will be used to summarize categorical demographic information of the participants surveyed. The primary outcome will be the global satisfaction score on the AIMS with secondary outcomes being the derived AIMS subscales. AIMS subscales will be derived from barriers cited by focus group participants and confirmed through factor analytic procedures conducted during the AIMS pilot test. Projected subscales will include service accessibility, results reporting procedures, staff interpersonal skills, perceived technical competence of staff, and global satisfaction. To model the global AIMS scores on individuals adjusting for individual factors (age, race/ethnicity, etc.), linear regression models will be developed. Similar models will be developed for AIMS subscale scores.

Using global patient satisfaction as the primary outcome variable, we also then conduct comparison of AIMS survey characteristics between women who sought services within and outside of the Indian Health Service system. This will be done by averaging the global AIMS scores for participants with an Indian Health Service-sponsored mammogram and those with a non-Indian Health Service-sponsored mammogram. Similar averaging will be done for each AIMS subscale to obtain global AIMS subscale scores.

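### Concurrent validity is planned as a correlation between two AIMS scores: this does not meet the protocol's own definition and, read literally, is inflated by overlap

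*Protocol article*

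**What the plan says.** The Concurrent Validity section of the protocol article defines the concept by what the survey's results must agree with. The wording is "related to the scores on another instrument administered at the same time, or to some other criterion variable at the same time". It then gives the analysis: "We will assess concurrent validity by correlating the sum of the subscale scores for each respondent with their score on the general scale".

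Three other sections bear on what these two scores are:

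- **Development of an American Indian Mammography Satisfaction (AIMS) Survey:** "A global satisfaction score will be obtained by summing all subscale scores". Answers are given numerical values and summed within each scale, so these are raw sums. Of the earlier validated questionnaire on which AIMS is partly based, it says "This instrument includes 6 subscales"; general satisfaction is one of the six. It expects AIMS to have further subscales.
- **Construct/Discriminant Validity:** "Scores on the general satisfaction subscale will be used as the outcome variables and other subscale scores will be used as predictor variables".
- **Mammography Satisfaction Variation:** "Projected subscales will include service accessibility, results reporting procedures, staff interpersonal skills, perceived technical competence of staff, and global satisfaction".

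The Data Analysis section names no other instrument and no criterion outside AIMS for any validity analysis.

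**The concern.** There are two problems, and the first does not depend on how the second is settled.

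1. **No criterion.** The definition asks for something other than the instrument under test. The analysis supplies a second score from the same instrument. A correlation between parts of one questionnaire shows that the parts move together. It does not show that the questionnaire agrees with anything else.
2. **Overlap.** If the general satisfaction subscale is one of the scores summed, it is correlated with a total that contains it. The shared items then produce a positive coefficient even when the general subscale is unrelated to everything else in the survey.

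Aim 2 is to validate the survey. The other quantitative checks (Cronbach's alpha, the regression among subscales, the factor analysis) are also internal to AIMS. A coefficient reported as concurrent validity would therefore be taken as the one piece of criterion evidence, and the study as described does not collect any.

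**Working it through.** **Step 1: is the general scale inside the sum?** The protocol states no figure for this correlation, so there is none to reproduce. The wording points to inclusion:

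- General or global satisfaction is called a subscale under both Construct/Discriminant Validity and Mammography Satisfaction Variation.
- The only subscale sum that the protocol defines runs over all subscales.
- The discriminant-validity section says *other* subscales when it leaves the general one out. The Concurrent Validity section, directly before it, has no such word.

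Inclusion is thus the literal reading, but it is an inference.

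**Step 2: size of the overlap effect.**

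Inputs from the protocol:
- k = 5 projected subscales, or 6 as in the parent instrument, with more expected
- n = 300 (Sample Size Justification)

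Assumptions not in the protocol:
- k up to 10
- a common correlation ρ between subscales, 0 to 0.5
- a ratio s of the general subscale's SD to that of each other subscale, 0.25 to 1.5

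Let m = k − 1, let G be the general subscale and O the sum of the others, each with SD 1.

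- Overlap kept: r(G, G+O) = (s² + ρsm) / (s·√[m + m(m−1)ρ + s² + 2ρsm])
- Overlap removed: r(G, O) = ρm / √[m + m(m−1)ρ]

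With unrelated subscales (ρ = 0) the first reduces to s / √(m + s²) and the second to 0. For k = 5 and s = 1 this is 1/√5 = 0.447; for k = 6 it is 1/√6 = 0.408; for k = 5 and s = 0.5 it is 0.5/√4.25 = 0.243.

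| ρ = 0, overlap kept | s = 0.25 | s = 0.5 | s = 1 | s = 1.5 |
|---|---|---|---|---|
| k = 5 | 0.124 | 0.243 | 0.447 | 0.600 |
| k = 6 | 0.111 | 0.218 | 0.408 | 0.557 |
| k = 10 | 0.083 | 0.164 | 0.316 | 0.447 |

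Every cell is 0 once the overlap is removed.

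For related subscales, with k = 5 and s = 1:

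| ρ | Overlap kept | Overlap removed |
|---|---|---|
| 0.2 | 1.8/√9 = 0.600 | 0.8/√6.4 = 0.316 |
| 0.3 | 2.2/√11 = 0.663 | 1.2/√7.6 = 0.435 |
| 0.5 | 3/√15 = 0.775 | 2/√10 = 0.632 |

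**Step 3: how it would look in the data.** In 5,000 simulated surveys with n = 300, k = 5, s = 1 and unrelated subscales:

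- Overlap kept: mean 0.447, 95% range 0.35 to 0.53, nominally significant in 100% of runs.
- Overlap removed: mean 0.00, 95% range −0.11 to 0.11, nominally significant in 4.6% of runs.

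By Fisher's z, the chance of nominal significance at n = 300 is Φ(atanh(r)·√297 − 1.96). This is about 99% for r = 0.243 and about 57% for r = 0.124.

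**Step 4: if the general scale is left out.** The artefact disappears, but both scores still come from AIMS, so the definition is still not met. The result would also add little. The next section already regresses general satisfaction on the other subscales, and the absolute correlation with their unweighted sum cannot exceed that regression's multiple R.

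**The case against.** The strongest reply is that the overlap is read into the text. The sentence sets the subscale sum against the general scale and does not say that all subscales are summed. The next section makes the same contrast with the general subscale excluded, and a condensed article may leave that detail to the full plan. This stands as far as it goes: the overlap is probable, not certain. It does not answer the first problem, because the stated method uses AIMS scores alone under either reading.

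Three stronger readings are tempting, and the document does not support them.

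- **A sizeable coefficient is guaranteed, or the check cannot fail.** The built-in value depends on the number of subscales and on the general scale's relative spread. Raw answers are summed, so a short general scale may have a small SD and more subscales lower the value further. A positive floor also assumes that the subscales are not substantially negatively related. The protocol sets no pass mark.
- **The correlation is exactly 1.** This needs the general scale to mean the total score. The next section speaks of a general satisfaction subscale, which makes that reading implausible.
- **The Aim 3 result is undermined.** The comparison of women inside and outside the Indian Health Service does not use this coefficient. No estimate, test or sample size there changes.

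It is also fair to say that this is one strand among several: a nine-expert content review, face validity in 50 pilot women, alpha, regression and factor analysis. These have value, but none is a criterion in the sense the protocol defines.

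**Conclusion.** The point holds in a limited form. The planned analysis is an internal correlation labelled as concurrent validity, and it does not meet the definition given in the same paragraph. That part is independent of any assumption.

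On the literal reading the coefficient is also inflated by construction. For unrelated subscales it is about 0.41 to 0.45 with five or six subscales of similar spread. Across five to ten subscales it is about 0.08 to 0.24 when the general scale has a quarter to half the SD of the others. Either way the value without overlap is 0. The size rests on assumed spreads and correlations that the protocol does not give, and on the inference that the general scale is in the sum. The consequence is confined to the validity evidence for Aim 2.

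**What to change.** 1. State that the general satisfaction subscale is correlated with the sum of the *other* subscales, and report the result as an internal subscale correlation. This costs nothing.
2. Then choose one of two courses:
   - To claim concurrent validity as defined, add a short criterion measure administered with the survey but not scored into AIMS, and correlate the AIMS global score with it. The choice needs care: AIMS is built from existing instruments, and the Background says that the parent questionnaire's general satisfaction subscale already touches on intention to return for screening. A criterion of that kind must not duplicate scored items. The cost is a few extra items, which pulls slightly against the aim of a brief survey.
   - Otherwise, drop the concurrent-validity claim and describe the evidence as content-based and internal.

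The survey is still to be written and piloted, so criterion items can be added before the form is locked (Survey Form Development). They cannot be recovered once data collection is over.
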